| NUMBER OF SUBJECTS REQUIRED (PATIENTS, CONTROLS IF ANY) | Number of subjects required   - Main objective: with 50% responders to the standard spa therapy at 6 months [1], a power of 80%, and an alpha risk of 5%, 135 patients per group are required to significantly demonstrate the non-inferiority of the active spa therapy with a lower confidence limit of the difference in proportions of 15%. Considering that the number of patients lost to follow-up may be 5%, a total of 284 patients is needed in the trial. |
| LENGTH  DURATION | Expected inclusion period: January 2012 to the end of October 2012, i.e., 10 months  Duration of participation (including follow-up period): for a patient, 6 months from the beginning of the treatment  Total duration (including data analysis time): from December 2011 to mid-October 2013, i.e., 2 years |
| INVESTIGATION PROCEDURE DIFFERENCES FROM USUAL CARE | Spa therapy is performed according to the usual scheme for the "classical spa therapy”. The "active spa therapy” follows a pattern with fewer thermal care sessions, which are replaced by functional rehabilitation sessions by physiotherapists according to usual techniques.  The Nancy Thermal site does not yet have thermal approval and this study is carried out with this objective in mind. The chemical qualities of sodium chloride-containing water are identical to those of the Amnéville les Thermes spa.  Visits are made at inclusion, at the beginning of the cure, at 3 and 6 weeks and at 3 and 6 months. |
| EVALUATION OF RESEARCH BENEFITS AND RISKS | - The expected benefits are a reduction in pain, functional discomfort, and drug use and an improvement in quality of life.  - Adverse reactions that can be experienced with thermal treatment are rare, most often minor and transient. They are traditionally observed during the thermal treatment period and are then part of what is usually called the "thermal crisis": it is mainly a question of fatigue, awakening of certain pains during the thermal treatment phase, unusual sweating and insomnia. These effects rarely require the cessation of thermal treatments.  More serious health problems are possible with thermal treatment but remain exceptional: heart problems, infections linked to bacteria that may be present in warm waters (among them Legionella infection). |

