**3. RESEARCH OBJECTIVES**

The purpose of this study is to compare the 6-month efficacy of two types of spa therapy: "standard spa therapy" (spa therapy delivered 6 days out of 7 for 3 consecutive weeks) and "active spa therapy” successively combining iterative spa sessions (3 sessions per week for 3 weeks) then specific re-education (3 sessions per week for 3 weeks).

The main objective of the study is to compare the proportion of patients with a composite response criterion combining the MCII for pain and/or functional ability and the absence of knee surgery on the targeted knee at 6 months, according to two types of spa therapy ("standard spa therapy" and "active spa therapy") in symptomatic knee OA.

The secondary objectives are as follows:

- To compare the effectiveness of the two types of spa therapy on pain and function at the end of the spa therapy and at 3 months

- To determine the evolution of quality of life scores (OAKHQOL, SF-36), of fatigue, patient satisfaction, medication use and care, as well as the use of surgery in both types of spa therapy

- To describe the effectiveness of standard spa therapy in Nancy Thermal on pain and functional abilities by an analysis of the before and after effect

- To describe the postural anomalies encountered with knee OA by a posturographic study and to evaluate the evolution of these anomalies according to the type of spa therapy and over time.

- To study the predictive factors of response to spa therapy (socio-demographic data, clinical, radiographic, ultrasonography and posturographic) at 3 and 6 months.

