**Table: Follow-up**

|  | **Selection inclusion** | **V0** | **V1**  **3** weeks | **V2**  **6** weeks | **V3**  **3 months** | **V4**  **6 months** |
| --- | --- | --- | --- | --- | --- | --- |
| Inclusion  Zelen randomization  Consent | X  X  X |  |  |  |  |  |
|  |  |  |  |  |  |  |
|  |  |  |  |  |  |  |
| Sociodemographic data | X |  |  |  |  |  |
| History of OA | X |  |  |  |  |  |
| Clinical examination | X |  |  |  |  |  |
| X-ray | X |  |  |  |  |  |
| Ultrasonography | X |  |  |  |  |  |
| Treatment | X | X | X | X | X | X |
| VAS pain | X | X | X | X | X | X |
| Clinical follow-up |  | X | X | X | X | X |
| WOMAC |  | X | X | X | X | X |
| Quality of life |  | X | X | X | X | X |
| Posturography |  | X | X | X | X | X |
| 6-minute walking test |  | X | X | X | X | X |
| Care consumption |  | X | X | X | X | X |
| Adverse reactions |  |  | X | X | X | X |
| Satisfaction, heiQ |  |  | X | X | X | X |

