**5. INCLUSION AND EXCLUSION OF PEOPLE FROM RESEARCH:**

5.1. INCLUSION CRITERIA

The patients with knee OA:

- Meeting the criteria for knee OA of the ACR (*)
- Uni- or bilateral OA
- Symptomatic: VAS pain > 3 on a scale of 0 to 10
- Radiological femoro-tibial knee OA³ stage 2 of the Kellgren and Lawrence classification
- With consent
- Preliminary medical examination

* The diagnostic criteria used are those of the ACR [Altman 1986]:

- Knee pain and at least 1 of the following three criteria:
  - Age > 50 years old
  - Morning stiffness < 30 min
  - Crepitus on active motion
- The presence of osteophytes on knee X-rays

(sensitivity 94%, specificity 87%)

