**9. STATISTICS**

**Number of subjects required**

- Main objective: with a 50% percentage of responders to standard spa therapy at 6 months [1], a power of 80%, and an alpha risk of 5%, 135 patients per group are required to significantly demonstrate the non-inferiority of the active spa therapy with a lower confidence limit of the difference in proportions of 15%. Considering that the number of patients lost to follow up may be limited to 5%, a total of 284 patients should be included in the trial.
- For the secondary objective of comparing 3-month responders, the percentage of responders being higher than at 6 months, the number of subjects needed is lower: with a 60% percentage of responders to standard spa therapy at 3 months, a power of 80%, an alpha risk of 5%, 77 patients per group are required to significantly demonstrate the non-inferiority of the active spa therapy with a lower confidence limit of the difference in proportions of 19%. For demonstrating an effect of spa therapy sufficient to obtain thermal approval, the evidence of an effect size of 0.3 in an analysis of the before-and-after effect in the same group [6] with 80% power and 5% alpha risk with a test, 90 patients are needed in each group.

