**Descriptive statistics**

Qualitative criteria will be described by their number and percentage and quantitative criteria by average, standard deviation or median and interquartile range (25th percentile- 75th percentile).

Results after treatment will be described by the number and percentage of responders according to the composite criterium, MCII pain, MCII function, PASS criteria and by the evolution of scores (means, standard deviation of differences) of self-questionnaires measuring health status.

To compare the evolution before and after treatment, matched t-tests will be carried out for quantitative assessment criteria and by testing McNemar for binary outcome criteria.

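### Section 9 sizes an uncontrolled before-after test to demonstrate a spa effect for thermal approval; the design supports only a description of change, which is all that the matching objective asks for

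*Protocol*

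**What the plan says.** The protocol summary, under differences from usual care, gives approval as a purpose of the trial: "The Nancy Thermal site does not yet have thermal approval and this study is carried out with this objective in mind". Its list of expected outcomes repeats this.

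Section 9, under the number of subjects, turns that purpose into a powered test: "For demonstrating an effect of spa therapy sufficient to obtain thermal approval, the evidence of an effect size of 0.3", to be found "in an analysis of the before-and-after effect in the same group", with 80% power, 5% alpha and 90 patients in each group. The same section, under descriptive statistics, names the method: "To compare the evolution before and after treatment, matched t-tests will be carried out for quantitative assessment criteria".

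The matching secondary objective in section 3 is more modest: "To describe the effectiveness of standard spa therapy in Nancy Thermal on pain and functional abilities by an analysis of the before and after effect". The summary says the same.

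Entry requires current pain (section 5.1): "Symptomatic: VAS pain > 3 on a scale of 0 to 10". The follow-up table in section 4.2 records pain at selection, at V0 and at every later visit ("VAS pain | X | X | X | X | X | X"), while WOMAC starts at V0. Sections 4.2 and 7.2 place the pre-treatment assessment at V0.

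**The concern.** Section 9 gives the before-after analysis a property that the design does not have. Demonstrating an effect of a treatment needs a contrast with what would have happened without it. Here both randomised arms receive thermal care, so the only reference for the before-after change is zero. Zero change is not a credible expectation without spa care. The patients are recruited while in pain, cannot be blinded, continue their usual treatment (section 6) and may take any further medication or care (summary, study design). Each of these can move the mean away from zero.

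At stake is a secondary aim, but one tied to a declared purpose of the trial. An approval report written from section 9 could present non-specific improvement as a demonstrated effect. The mismatch between demonstrating (section 9) and describing (section 3) lies within the protocol itself and does not depend on what a separate analysis plan may add.

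**Working it through.** **Inputs from the protocol (section 9).** Effect size 0.3, power 80%, alpha 5%, 90 patients per group, paired t-test; 135 per group for the primary analysis. The standardiser of the 0.3 is not stated; I take it as mean change divided by SD of change. Sidedness is not stated for this test.

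**Step 1: reproduce the 90.**
- Normal approximation, two-sided: n = ((1.960 + 0.842)/0.3)² = 87.2, so 88.
- Exact noncentral t, two-sided: n = 90, with power 80.4%.
- One-sided: 69 (normal) or 71 (t), which does not match.

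The stated figure is therefore right for a two-sided paired t-test against zero.

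**Step 2: smallest observed change that is significant.** This is t(0.975, n−1)/√n.
- n = 90: 1.987/9.487 = 0.21 SD of change.
- n = 135: 1.978/11.619 = 0.17 SD of change.

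**Step 3: chance of a significant result if the spa does nothing.** Let d be the non-specific improvement in SD of change. The test statistic then follows a noncentral t with noncentrality d√n. The protocol gives no value for d, so a range is assumed.

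| Assumed d | n = 90 | n = 135 |
|---|---|---|
| 0.1 | 16% | 21% |
| 0.2 | 47% | 64% |
| 0.3 | 80% | 93% |

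The last row is the planned power itself: a drift of 0.3 SD from any source is detected as readily as a spa effect of 0.3 SD. More patients make this worse.

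**Step 4: how much of d can come from the pain threshold.** Assume normally distributed pain with mean 40–60 mm and SD σ of 20–25 mm before selection, and a cut at 30 mm. Let λ be the standardised excess of the selected mean.
- Expected fall from selection to V0: (1 − r₁)σλ.
- Expected fall from V0 to follow-up: (r₁ − r₂)σλ.

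Here r₁ and r₂ are the correlations of the selection value with V0 and with follow-up. For mean 40 and SD 20, σλ = 10.2 mm.
- With V0 as the before value and r₁ = r₂, the fall is 0.
- If the correlation drops from 0.8 to 0.6, the fall is 0.2 × 10.2 = 2.0 mm, or 0.17 SD of change. Over the assumed means and SDs it reaches at most about 0.18 SD.

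From V0, the threshold contributes between nothing and a modest amount. Natural course, expectation and other care are not bounded by this calculation.

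**The case against.** The strongest reply is that the objective is already descriptive, that the t-tests stand under a descriptive heading, and that the stronger wording occurs only in one sample-size sentence. That is accurate and limits the point to that claim. It does not remove it, because the sentence carries its own power calculation and names approval as the use.

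Four stronger readings are tempting and are not supported.

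- A reader might infer that the entry threshold alone could produce most of the 0.3. That needs the selection pain score as the before value. Sections 4.2 and 7.2 point to V0, from which this regression is zero unless the correlation decays.
- A reader might treat selection to V0 as an untreated control period and test the later change against it. Usual treatment continues, so the interval is pre-spa, not untreated. It also absorbs the regression caused by the threshold. Subtracting it would bias the spa effect downward by 1.2 mm (mean 50, SD 20, r = 0.8) to 5.1 mm (mean 40, SD 20, r = 0.5). Its length is not fixed, it exists for pain only, and expectation effects would remain. Assuming equal SDs of change and a correlation of −0.5 to 0 between the two changes, power with 90 patients would be 37–51%.
- A reader might conclude that an ineffective cure would win approval. What the approving body requires is not in the documents, and section 6 shows that the request also depends on water sampling.
- A reader might carry the point over to non-inferiority. The protocol rests the comparator on a cited randomised multicentre trial of the same care scheme, and never on the before-after change.

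**Conclusion.** The point holds as a mismatch between claim and design. The sample size is correct for the test named, but a significant result would show that patients changed, not that the spa changed them. Its size depends on the unknown non-specific improvement: over an assumed 0.1 to 0.3 SD of change, the chance of a significant result with no spa effect is 16% to 80% at 90 patients. The calculation assumes that 0.3 is expressed in SDs of change and that the test is two-sided, which the reproduction supports. It concerns a secondary aim and leaves the primary comparison untouched.

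**What to change.** In section 9, number of subjects, replace the claim of a demonstrated effect with *estimating the observed, uncontrolled change after spa therapy*. Add that this change is reported with its confidence interval and is not attributed to spa therapy in the approval report. This brings the section into line with section 3. The 90 patients can stay as a precision statement: the 95% interval has a half-width of about 0.21 SD of change (step 2).

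Under descriptive statistics, name V0 as the before value for all paired comparisons.

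Optionally, show the selection-to-V0 change in pain beside it, with its interval length, labelled as a pre-spa change available for pain only. It should be neither subtracted nor used as the reference for a test.

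The cost is a few sentences, with no new visits, data or patients. The downside is a less favourable claim for the approval file.

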**Descriptive statistics**

Qualitative criteria will be described by their number and percentage and quantitative criteria by average, standard deviation or median and interquartile range (25th percentile- 75th percentile).

Results after treatment will be described by the number and percentage of responders according to the composite criterium, MCII pain, MCII function, PASS criteria and by the evolution of scores (means, standard deviation of differences) of self-questionnaires measuring health status.

To compare the evolution before and after treatment, matched t-tests will be carried out for quantitative assessment criteria and by testing McNemar for binary outcome criteria.

**Comparison of groups**

The trial being a non-inferiority trial, the main analysis will be per protocol to be conservative by increasing the contrast between the groups.

Main objective

The active spa therapy will not be considered inferior to the standard spa therapy if the lower bound of the confidence interval at 90% of the difference between the 2 groups (active spa therapy minus standard spa therapy) for the main outcome criterion (percentage of respondents according to the composite criterion) is not less than 15%[1]. After verification of the randomization that could be unbalanced owing to the Zelen randomization mode, the final analysis will be adjusted if necessary on the variables that differ between the 2 groups.

Secondary objectives

- The same analyses will be repeated for the MCII composite criterion, pain and function at 3 months and for PASS criteria.

- To determine the predictive factors of spa therapy response, a bivariate analysis will be performed using chi-square tests (or Fisher exact tests depending on the number) for discrete variables, and Student t-tests, ANOVA or Wilcoxon tests for quantitative variables. The parameters significant on bivariate analyses (at the conservative threshold of p=0.1) will then be introduced into a stepwise multiple logistic regression.

A value of p<0.05 will be considered statistically significant.

The statistical analysis will be carried out by the Centre for Clinical Epidemiology by using SAS v9.2 (SAS Inc., Cary, NC).

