| secondary outcome criteria | Secondary criteria   - Percentage of patients reaching MCII (pain, function and composite score) at the end of the treatment and at 3 months - Percentage of patients reaching the Patient Acceptable Symptom State (PASS) (pain and function) at 3 and 6 months. - Evolution of quality of life scores (OAKHQOL, SF-36) at 3 and 6 months - Evolution of VAS-fatigue, VAS-pain at 3 and 6 months - Evolution of WOMAC scores (function) at 3 and 6 months - Patient satisfaction (overall VAS or Health Education Impact Questionnaire **(**heiQ) module 9) at 3 and 6 months - Evolution of drug and care consumption, use of surgery - 6-minute walking test [43] - Evolution of posturography parameters: modification of the length travelled and/or the area covered by the pressure centre of the feet following the removal or disruption of sensory inputs, somesthesics of balance in distorted visual situations and static and dynamic positions [4] - adverse reactions |
| METHODOLOGY/ STUDY DESIGN | This is a single-centre, randomized, single-blind clinical trial of non-inferiority comparing "standard spa therapy" and "active spa therapy" in knee OA.  The patients in the standard spa therapy group will undergo a “classical spa therapy” according to the standardised care protocol defined in Thermarthrosis [1], that is, 1 daily session, 6 days a week for 3 weeks. The patients in the active spa therapy group will undergo therapy comprising thermal treatments of the classical spa therapy at a rate of 3 sessions per week for 3 weeks, followed by proprioceptive re-education and muscle strengthening at a rate of 3 sessions per week for 3 weeks. In both groups, patients will be allowed to take any additional medication and care that their referring physician deems necessary.  Randomization will be blinded and will use the Zelen method (randomization before consent is obtained).  Patients will be examined at 3 and 6 months by an evaluating physician, independent of the spa, who will be blinded to the patient's treatment group.  As a non-inferiority trial, the analysis will be per-protocol. |

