| STATISTICAL ANALYSIS | **Descriptive statistics**  **Comparison of groups**  The trial being a non-inferiority trial, the main analysis will be a per-protocol analysis to be conservative by increasing the contrast between the groups.  Main objective  The active spa therapy will not be considered inferior to the standard spa therapy if the lower bound of the confidence interval at 90% of the difference between the 2 groups (active spa therapy minus standard spa therapy) for the main outcome criterion (percentage of respondents according to the composite criterion) is not less than 15%. After verification of the randomization that could be unbalanced due to the Zelen randomization mode, the final analysis will be adjusted if necessary on the variables that differ between the 2 groups.  Secondary objectives  - The same analyses will be repeated for the MCII composite criterion, pain and function at 3 months, and PASS criteria.  - To determine the predictive factors of spa therapy response, a bivariate analysis will be performed using chi-square tests (or Fisher exact tests depending on the number) for discrete variables and Student t-tests, ANOVA or Wilcoxon tests for quantitative variables. The parameters significant on bivariate analyses (at the conservative threshold of p=0.1) will then be introduced into a stepwise multiple logistic regression.  P<0.05 will be considered statistically significant.  The statistical analysis will be carried out by the Centre for Clinical Epidemiology by using SAS v9.2 (SAS Inc., Cary, NC). |
| EXPECTED FALLBACK | To be able to offer different types of spa therapy in order to adapt to patients' preferences.  Propose a spa therapy that can be performed externally near the patient’s home.  Offer a less tiring cure.  Obtaining thermal approval for the Nancy Thermal site. |

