**4.3. DESCRIPTION OF THE MEASURES TAKEN TO REDUCE AND AVOID BIAS**

Randomization

Most literature reviews emphasize the importance of blinding of the assessor [44,45,46,47] and randomization [48,49,50] in a therapeutic trial. In the context of thermal care, it is impossible to blind the patient, which can lead to a bias of therapeutic preference [51]. The Zelen randomization method (randomization method before consent is obtained) must allow for reducing this bias. This method has been used successfully in the past [52,53]. For some, it has the additional advantage of reducing the number of refusals to enter the study [54]. A review published in 2006 shows that among 58 studies, this method was more frequently used to limit bias than to increase recruitment [55]. This method does not contradict the rules of ethics and is widely used in many studies.

Because patients cannot be completely blinded, randomization will be according to the Zelen method [51]. During the inclusion visit, patients will be informed that the purpose of the research is to study the effectiveness of the care provided during spa therapy. The content of spa therapy will not be explained in detail right away and randomization will occur before consent is obtained. In the event of refusal after allocation of the intervention group (e.g., the patient not wishing to undergo care for 6 weeks), the patient will be assigned to the other group. An information letter and a consent specific to each group will be proposed.

Randomization will be performed centrally and independently by use of a computer program at the Centre for Clinical Epidemiology (CIC EC). The randomization group will be available during the selection visit.

(b) Blinding methods.

The assessor will be blinded to the treatment group at 3 and 6 months.

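### The main analysis is per protocol and is called conservative, but refusers are moved to the other arm, so the set is selected by preference and not reliably conservative

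*Protocol*

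**What the plan says.** The protocol names the main analysis set three times. Section 9 (Comparison of groups) says that "the main analysis will be per protocol to be conservative by increasing the contrast between the groups". The statistical analysis entry of the summary says the same: "the main analysis will be a per-protocol analysis to be conservative by increasing the contrast between the groups". The study design entry of the summary is shorter: "As a non-inferiority trial, the analysis will be per-protocol". None of the three names an analysis by allocated arm, either co-primary or supportive.

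Section 4.3 (Randomization) adopts the Zelen method: "randomization will occur before consent is obtained". If a patient then refuses the allocated programme, "the patient will be assigned to the other group". The example given is "e.g., the patient not wishing to undergo care for 6 weeks", which can arise only in the active arm, since standard therapy lasts 3 weeks.

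The protocol does not define the per-protocol set. It also does not say whether a switched patient is dropped from it or counted in the arm received. One safeguard is stated, in section 9 and in the summary: after checking for imbalance caused by the Zelen method, "the final analysis will be adjusted if necessary on the variables that differ between the 2 groups".

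**The concern.** Per protocol is usually preferred in a non-inferiority trial because switching and poor adherence make the arms look alike, and removing those patients restores the contrast. That argument holds when removal is unrelated to prognosis. Here removal follows the patient's own view of one programme. The programmes differ in length (3 or 6 weeks), frequency (6 or 3 sessions a week) and time of day (morning or afternoon, section 4.5). Patients who would refuse active therapy leave that arm, while patients of the same kind who were allocated to standard stay there unidentified. The two remaining groups are then no longer the randomised groups.

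The trial's only confirmatory conclusion is at stake. If those who leave active therapy would have responded less often, the active arm looks better than it is, and non-inferiority can be declared when the true deficit is at the margin.

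**Working it through.** **The plan's own figure.** Inputs from section 9: 50% responders on standard at 6 months, 80% power, 90% confidence interval (one-sided 5%), and a margin of 15 points, printed without a sign and read here as -15.

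n per arm = 2 × 0.5 × 0.5 × (1.645 + 0.842)² / 0.15² = 137.4, so 138. The plan states 135, which is within 3%. Power at 135 is 79.4%. The total also agrees: 270 / 0.95 = 284.2, against 284 stated. The sample size is not in dispute.

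**Assumed inputs.** The protocol gives no refusal rate and no prognosis for refusers. Let r be the share of patients allocated to active who refuse it and receive standard, and g the number of points by which refusers respond less often than acceptors on either programme. The true effect is -15 points in everyone, with 135 evaluable patients allocated per arm.

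- Acceptors on standard respond at a = 0.50 + r·g, and refusers at a - g, so the overall rate on standard is 0.50.
- Switchers dropped: active a - 0.15 with n = 135(1 - r); standard 0.50 with n = 135.
- Switchers counted as treated: active as above; standard (0.50 + r(a - g)) / (1 + r) with n = 135(1 + r).
- By allocated arm: difference = -0.15(1 - r), with n = 135 in each arm.
- Probability of declaring non-inferiority = Φ((d + 0.15)/SE - 1.645), where d is the expected difference and SE the unpooled standard error.

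**Worked case, r = 15%, g = 20 points.** a = 0.53 and refusers respond at 0.33.

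- Dropped: 0.38 against 0.50, d = -0.12. SE = √(0.38·0.62/114.75 + 0.25/135) = 0.0625. Φ(0.480 - 1.645) = 12.2%.
- As treated: standard = (0.50 + 0.15·0.33)/1.15 = 0.478, d = -0.098, SE = 0.0605. Φ(0.863 - 1.645) = 21.7%.
- Allocated arm: d = -0.1275, SE = 0.0599. Φ(0.376 - 1.645) = 10.2%.

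**False non-inferiority when only active is refused (nominal 5%)**

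| r | g (points) | Dropped | As treated | Allocated arm |
|---|---|---|---|---|
| 10% | +20 | 9.4% | 14.9% | 8.2% |
| 15% | +20 | 12.2% | 21.7% | 10.2% |
| 20% | +20 | 15.5% | 28.9% | 12.6% |
| 15% | +10 | 8.0% | 11.3% | 10.2% |
| 15% | 0 | 5.0% | 5.0% | 10.2% |
| 15% | -20 | 1.6% | 0.6% | 10.2% |

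Simulation agrees within a few tenths of a point, except that by allocated arm it runs slightly lower (about 8-12% for r = 10-20%).

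**Other refusal patterns, by simulation (g = +20)**

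| Refuse active / standard | Dropped | As treated | Allocated arm |
|---|---|---|---|
| 7.5% / 7.5% | 5.0% | 4.9% | 9.9% |
| 5% / 10% | 3.5% | 2.7% | 10.0% |
| 0% / 15% | 1.6% | 0.6% | 10.0% |

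**Requiring both sets, switchers dropped (simulation).** With only active refused and g = +20, false non-inferiority is about 7%, 9% and 10% at r = 10%, 15% and 20%.

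**Success when the arms are truly equal, r = 15% (simulation).** With no prognosis gap, per protocol alone succeeds 76.6% of the time and the joint rule 74.1%, a fall of 2.5 points. With g = +20 the figures are 88.3% and 78.2%. Most of that 10-point fall is the removal of bias that favoured active.

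**The case against.** The strongest reply is that the direction of bias is not established, and this stands. The inflation needs two things together: refusal falling mainly on active, and refusers doing worse. The 6-week refusal in section 4.3 is only an example. The protocol's background reports that patients find the conventional programme tiring, intensive and hard to fit in, which points towards refusal of standard. With balanced refusal, refusal mainly of standard, or no prognosis gap, per protocol is at or below 5%, while analysis by allocated arm is near 10%. In those cases the protocol's rationale is right.

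A reader might therefore infer too much in two ways. One is that the plan will falsely show non-inferiority; the documents give neither a refusal rate nor refusers' prognosis, so only *can* is supported. The other is that intention to treat should replace per protocol; the tables show that it is too lenient alone, because switching dilutes the difference.

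The planned adjustment is a real safeguard but a partial one. It covers measured factors only, is chosen after imbalance is seen, and cannot recreate the randomised comparison.

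Finally, calling per protocol the main analysis leaves room for others, and a separate analysis plan may add one by allocated arm. That does not answer the point. The protocol itself fixes the main set, gives a reason for it, and sets a switching rule under which that reason may fail.

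**Conclusion.** The point holds in a limited form. The stated main analysis rests on a set selected partly by patient preference, and the claim that it is conservative is not reliable under the protocol's own switching rule. The size depends on assumptions that the protocol cannot supply. If 10-20% refuse active only and respond 20 points less often, false non-inferiority at a 15-point deficit is about 9-15% with switchers dropped and 15-29% with switchers counted as treated. It is about 5% with no prognosis gap or balanced refusal, and lower if mainly standard is refused. Because the handling of switchers is left open, the same data could be read at either end of that adverse range. No single analysis set is safe in all these cases.

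**What to change.** In section 9 and both summary entries:

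- State that patients who switch after allocation are excluded from the per-protocol set and are not counted in the arm received.
- Add an analysis of all consenting patients in the arm first allocated, whatever they received. Note that consent follows allocation and uses a form specific to each group, so this set is close to, but not fully, as randomised.
- Claim non-inferiority only if the lower limit of the 90% interval lies above -15 points in both sets.
- Report refusals and switching by allocated arm.
- Qualify the conservative statement: per protocol counters dilution from switching, but is conservative only if switching is unrelated to prognosis or the resulting bias runs against active therapy.

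The cost is one further analysis of data already collected and about 2-3 points of power when refusal is unrelated to outcome. The apparent fall is larger (about 10 points at 15% refusal and a 20-point gap) where per protocol is biased in favour of active. The joint rule limits the error, to about 7-10% in the adverse scenario, but does not bring it back to 5%, and the report should say so.
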